## Abstract

**Background: **Executive dysfunction appears to be related to increased recidivism. Of note is that sleep disturbances, which are highly prevalent in prisons, may attenuate executive functions. Thus, improving executive functions, either directly or indirectly through the improvement of sleep, may reduce recidivism. It is hypothesised that physical exercise, in the form of Running Therapy, has a direct positive effect on executive functions as well as an indirect effect through the improvement of sleep.

**Methods/Design: **Seventy two (N = 72) detainees in various penitentiary institutions in the Netherlands will be recruited in this study. A baseline measurement, including six neuropsychological tests of the Cambridge Neuropsychological Test Automated Battery (CANTAB), an assessment of sleep quality and duration using the Actiwatch (Actiwatch 2, Philips Respironics, Murrysville, PA, USA) and various other measurements will be administered before the start of the treatment. After 3 months of Running Therapy, participants will be assessed again with the same tests for neuropsychological and physical functioning. Primary outcomes are executive functioning and various sleep variables.

**Discussion: **This study will be the first to investigate the possible influence of Running Therapy on the cognitive functioning, sleep and aggression in prisoners.

## Background

International studies report that 35 to 67 percent of released prisoners are detained for reoffending within approximately 2 to 3 years
^1–
4^. These percentages show that the reduction of recidivism is of great importance to society, since crime carries a great (financial) burden
^5^.

The risk of reoffending appears to be negatively related to executive functioning
^6–
8^. Executive functions are higher order cognitive functions including planning, working memory, taking initiatives, set-shifting, attention, and impulse control
^9,
10^, and are crucial for self-regulation
^11^. Planning and goal-directed behaviour are essential for successful re-entry into society, as ex-prisoners face complex challenges such as finding housing and employment
^12^. Another important executive function is impulse control, which enables us to regulate and suppress aggressive behaviour, for example
^9^; reduced impulse control thus increases the risk of aggressive behaviour.

Executive functions may be improved by physical activity
^13,
14^. For example, brisk walking was found to improve impulse control in older adults
^14^. An increase in impulse control after participation in a physical activity programme is quite a consistent finding
^13,
15,
16^ and appears especially effective in sedentary people
^13^. Prison life consists mostly of passive leisure activities such as watching television
^17^, and physical inactivity is a hallmark of prison life in various countries
^18–
21^. So, a large percentage of the prison population has a sedentary lifestyle.

Closely related to both executive functioning and physical (in)activity is sleep. Sleep disturbances may diminish executive functioning
^22^, while increased physical activity may improve sleep
^23,
24^. Sleep disturbances are highly common in prison and are responsible for a relatively large part of prison health care use
^25,
26^.

Besides sleep disturbances, various psychiatric disorders are also highly prevalent in prisons, such as depression
^27^, anxiety disorders and ADHD
^28–
30^. These psychiatric disorders may also negatively affect sleep
^31^. Exercise, e.g. Running Therapy, may indeed reduce symptoms of depression and anxiety
^32^ and behavioural symptoms of ADHD
^33,
34^.

In sum, physical activity may positively influence executive functions directly, but also indirectly, through improved sleep. We therefore hypothesize that physical exercise, in the form of supervised Running Therapy, will improve executive functioning and sleep, and will reduce aggression in prisoners. Although a randomized controlled trial (RCT) would be the best option to test this hypothesis, our current study could be considered a pilot behavioural intervention trial. Conducting an RCT directly is not possible, as the participating prisons were currently not willing to withhold treatment for some prisoners (i.e. the control group). However, this pilot study may eventually lead to an opportunity to conduct an RCT.

## Methods and analysis

### Study design

This study concerns a prospective cohort study, measuring neuropsychological performance and sleep of detainees before and after receiving 3 months of Running Therapy. No further experimental intervention will take place, and this study does not interfere with or alter daily programs, treatments or any other environmental factors.

### Participants

Prisoners (male adults) of two Penitentiary Institutions in the Netherlands (i.e. PI Leeuwarden and PI Ter Apel) that are referred to Running Therapy by the psycho-medical staff will be recruited in this study. Various complaints or disorders may result in referral to Running Therapy, e.g. ADHD, sleep disturbances, anxiety disorders and depression. All participants in Running Therapy who speak sufficient Dutch or English will be approached and asked to participate in this study. In addition, we will attempt to approach those who do not speak Dutch or English by using a translation phone service often used in Penitentiary Institutions by the psycho-medical staff. As we are not allowed to interfere with daily practice in prison, participants will continue to receive treatment-as-usual from the prison care, which may entail changes in drug regimen or participation in other interventions. Participants may be excluded from Running Therapy when they sustain an injury or when they behave aggressively. Such decisions are made by the running therapist in concordance with the prison staff.

### Intervention

Running therapy is already part of the regular care in the Penitentiary Institutions where this study will be conducted. Prisoners are referred to Running Therapy by the psycho-medical staff, which consists of the psychologist, psychiatrist, physician and nursing staff. Of note is that this study does not make any modifications to the Running Therapy, and studies the intervention as is.

***Running Therapy.*** This aerobic exercise group-therapy consists of supervised running for 2 days per week and 1 day per week of unsupervised running. During the therapy, the therapist encourages participants to run at a moderate pace and keeps track of the goals and sub-goals of the participants. The main goal of the therapy is to be able to run consecutively for 30 minutes at a moderate pace, three times per week, which will be achieved after 15 weeks of Running Therapy (see Appendix A for the complete program). Of note is that the therapy does not solely consist of running, but also contains a social aspect (running in a group, talking with participants or the therapist) and a reward aspect (achieving sub goals).

### Setting

The Running Therapy is currently offered in two Penitentiary Institutions in the Netherlands, PI Ter Apel and PI Leeuwarden, and the study will take place in both these institutions.

### Measurements and procedures

Participants will undergo two measurements: a baseline measurement before starting with Running Therapy and a post measurement after 3 months of Running Therapy. The baseline measurement takes place over a single day and will take approximately 90 minutes in total. At the baseline measurement, anamnesis takes place and the participant will be assessed with a neuropsychological test battery, the Cambridge Neuropsychological Test Automated Battery (CANTAB). In addition, participants are given four questionnaires (see “Secondary Outcome Measures” for more information) to fill out in their own time, and are instructed to bring these with them to the first day of Running Therapy. Optionally, an Actiwatch (Actiwatch 2, Philips Respironics, Murrysville, PA, USA) will be handed to the participant, which will be worn for 7 consecutive days (for more information about the Actiwatch, refer to “Primary outcome measures – Sleep”.

After three months of participating in Running Therapy, the participant will undergo the same tests as taken when assessing the baseline measurement. The four questionnaires and the Actiwatch will again be handed out to the participant.

According to the policy of the Dutch Custodial Institutions Agency (DJI), we are not allowed to provide the participant with an incentive. However, the measurements will be planned during the moments in which participants are usually spending time in their cell. We have experienced that prisoners regard the measurements as a welcome change.

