### Statistical analysis

For the main research questions (i.e. does running therapy improve cognition and sleep?), a repeated measures AN(C)OVA will be conducted for the results on the CANTAB and for the various sleep variables, comparing the baseline results with the post-measurement results. The main analyses will be conducted according to the intention-to-treat principle. Missing data will be imputed using the multiple imputation function as provided in SPSS 21 (IBM Corp, Armonk, NY, USA).

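### The post-measurement is tied to continued participation, so the intention-to-treat analysis may lack data on men removed from therapy

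*Protocol article*

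**What the plan says.** Four statements in the protocol article bear on this point.

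- **Analysis set** (Statistical analysis): "The main analyses will be conducted according to the intention-to-treat principle".
- **Missing data** (Statistical analysis): "Missing data will be imputed using the multiple imputation function as provided in SPSS 21". The article describes no separate handling of men who leave therapy.
- **Timing of the second assessment** (Measurements and procedures): first given as "a baseline measurement before starting with Running Therapy and a post measurement after 3 months of Running Therapy", then more specifically: "After three months of participating in Running Therapy, the participant will undergo the same tests as taken when assessing the baseline measurement". The Abstract also counts the three months in Running Therapy. No section sets the assessment by calendar time from baseline or from the first session.
- **Leaving therapy** (Participants): "Participants may be excluded from Running Therapy when they sustain an injury or when they behave aggressively". On who decides: "Such decisions are made by the running therapist in concordance with the prison staff".

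The Background hypothesises that Running Therapy "will improve executive functioning and sleep, and will reduce aggression in prisoners" and links weak impulse control to a higher risk of aggressive behaviour. Response inhibition and decision-making impulsivity are among the primary CANTAB measures. Aggression is measured by a secondary self-report questionnaire.

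**The concern.** In a single-group study there is no randomised comparison to protect. Intention-to-treat can then only mean that every enrolled man counts, however long he stayed in therapy. That requires outcomes from men who leave, and the timing rule as worded does not reach them.

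If every observed post value comes from a man who stayed, multiple imputation has nothing from which to learn what happens after removal. Under missing at random it assigns removed men the change seen in stayers with similar observed data. The estimate is then essentially one for stayers, under an intention-to-treat label.

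Removal for aggression makes missing at random doubtful for some outcomes, because on the article's own reasoning such behaviour is connected with impulse control and aggression. If men removed for this reason do worse than comparable stayers, the pre-post change on those outcomes is overstated. There is no control group in which a similar loss could offset it. Assessments that were never made cannot be recovered by a later analysis plan.

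**Working it through.** **1. The plan's own figure.** Inputs from Sample size calculation: f = 0.15, alpha 0.05, power 0.80, one group, two measurements (m = 2), r = 0.6. For a within-subject F test the noncentrality is f² × N × m / (1 − r). At N = 72 this is 0.0225 × 72 × 2 / 0.4 = 8.1, with 1 and 71 degrees of freedom, and power is 0.8016. N = 71 gives 0.7960. The stated N = 72 reproduces, so the sample size arithmetic is not at issue. With two time points, f = 0.15 corresponds to a mean change of 2 × 0.15 = 0.30 SD, which is used below as the change in men who stay.

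**2. The all-enrolled mean.** Let p be the proportion removed and not retested, and c their true mean change in SD. Both are assumptions, since the article gives neither.

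- True mean over all enrolled = (1 − p) × 0.30 + p × c
- Estimate if removed men are imputed from stayers ≈ 0.30
- Overstatement = p × (0.30 − c)

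| p | c | True mean | Reported / true |
|---|---|---|---|
| 15% | +0.30 | 0.85 × 0.30 + 0.15 × 0.30 = 0.300 | 1.00 |
| 15% | 0 | 0.85 × 0.30 = 0.255 | 0.30 / 0.255 = 1.18 |
| 15% | −0.30 | 0.255 − 0.045 = 0.210 | 0.30 / 0.210 = 1.43 |
| 25% | −0.30 | 0.225 − 0.075 = 0.150 | 0.30 / 0.150 = 2.00 |

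The first row matters as much as the others: if removed men change as stayers do, there is no bias.

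**3. Does imputation behave this way?** It was simulated with N = 72, r = 0.6, 20 normal-regression imputations given the baseline value, Rubin's rules and 1,500 replicates.

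| Removed | Imputed estimate, c = 0 | True | Imputed estimate, c = −0.30 | True |
|---|---|---|---|---|
| 10% | 0.300 | 0.27 | 0.293 | 0.24 |
| 20% | 0.297 | 0.24 | 0.298 | 0.18 |
| 30% | 0.305 | 0.21 | 0.300 | 0.12 |
| 40% | 0.302 | 0.18 | 0.301 | 0.06 |

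The imputed estimate stays near 0.30 whatever happens to the removed men. This confirms the mechanism. It does not show that the bias exists in this trial, because the different change in removed men was built into the simulation.

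**The case against.** The strongest reply is that the key step is an inference. Men are excluded from therapy, not expressly from the study. Measurements and procedures opens by giving participants two measurements without exempting those who stop, and the intention-to-treat statement itself fits retesting of leavers. The sentence on three months of participating may simply describe the usual pathway. If leavers are tested at three months, the problem largely disappears. This objection stands as to certainty. It does not remove the need to correct the wording, because the more specific sentence makes testing conditional on taking part.

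Second, the imputation model is not fixed in the article. Baseline CANTAB results, the aggression questionnaire, the symptom checklist, previous incarcerations and medication could all enter it. If these explain removal, missing at random may be a fair approximation. That stands in part: baseline data cannot capture deterioration that begins after baseline.

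Third, the direction and size are assumed. Some removals will be for injury, where the direction is unclear, and an aggressive incident may reflect a high but stable baseline rather than worse change. No mechanism is offered for sleep, planning, working memory or set-shifting. This stands, and it limits the point to impulse control and aggression.

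Fourth, this is an uncontrolled pilot, and its Discussion says that an RCT must confirm any positive result. That lowers the stakes. Details of the imputation model and of sensitivity analyses may also properly sit in a statistical analysis plan that is not shown. When and whom to assess is different, because it governs data collection.

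A reader might infer that removed men are certainly not retested, or that the trial's result is biased towards benefit. The article supports neither statement.

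**Conclusion.** The point holds as an inconsistency of wording that carries a risk of bias. The intention-to-treat claim needs outcomes from all enrolled men. The assessment rule, read literally, supplies them only for men who stay, and imputation under missing at random would fill the gap with stayers' change. For impulse control and aggression this risks overstating benefit.

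The size cannot be derived from the article. In the cases worked above, the ratio of reported to true change runs from 1.00 to 2.00. All of them rest on an assumed removal rate, an assumed change in removed men, and the reading that those men are not retested. This is a cheap improvement worth making before data are collected, not a demonstrated flaw in the result. The rule for removing men from therapy is not questioned.

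**What to change.** **Assessment timing.** In Measurements and procedures, state that the post-measurement takes place three months after the first Running Therapy session for every enrolled participant who can still be reached, whether or not he is still in therapy. Record the reason for leaving.

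**Sensitivity analysis.** Repeat the imputation with the imputed post values of men removed for aggression shifted unfavourably by a delta, for example from 0 to 0.5 SD. The estimate moves by the imputed proportion times delta. With an assumed 15% so imputed, a delta of 0.5 lowers 0.30 to 0.30 − 0.15 × 0.5 = 0.225 SD.

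**If leavers cannot be assessed**, describe the result as one for men who completed three months and drop the intention-to-treat label.

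**Cost.** A wording change, a few extra assessments of about 90 minutes each with a portable test battery, and one extra imputation run. The therapy and the removal rule stay as they are. The estimated effect may be smaller. If all 72 men were measured and 10% or 20% had left therapy with no change, the diluted effect (f = 0.135 or 0.12) would give power of about 0.72 or 0.61 instead of 0.80.

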### Primary outcome measures

***Executive functions***

The CANTAB
^35^ is a computerised neuropsychological test battery and is used to assess the executive functions of the participants. A 12.1 inch touchscreen tablet is used to administer the test. In two tests, a two-buttoned press pad is used. Few studies have assessed the reliability and validity of the CANTAB. One older study, that included some, but not all tests included in the current study, showed that test-retest correlations are above 0.6 for most of the subtests
^36^. The main reason that we chose this battery is a practical one; neuropsychologically testing a prisoner can sometimes be logistically challenging. Using this highly portable test battery, that can be used in any room with a table and two chairs, provides us with the necessary flexibility to test participants anywhere the prison staff wants us to.

The following six CANTAB tests will be administered.

*SOC.* Stockings of Cambridge measures planning, and is similar to the commonly used Tower of London (TOL). The main outcome measure is the number of problems solved in the minimum number of moves.

*SWM.* Spatial Working Memory measures the ability to retain and manipulate information in the working memory and heuristic strategy. The main outcome measure is total number of errors made.

*SST.* The Stop Signal Task measures response inhibition. The main outcome measure is SSRT, which is calculated by subtracting the mean stop-signal delay (the time between the stimulus and the beep) from the median go reaction time (the median response time on trials without a beep).

*IED.* Intra-Extra Dimensional Set-Shift measures set-shifting and is similar to the commonly used Wisconsin Card Sorting Test. The main outcome measure is the total number of errors (adjusted for the number of trials conducted).

*CRT.* Choice Reaction Time is a simple reaction time assessment and is used to measure reaction time and attention. The main outcome measures are mean reaction time, and the difference in mean reaction time between the second and the first half.

*CGT.* The Cambridge Gambling Task measures decision-making impulsivity and risk-taking behaviour. The main outcome variables are measures of risk-taking, risk-adjustment, quality of decision making, delay aversion and overall proportion bet.

***Sleep***

*Actiwatch.* The Actiwatch AW2 (Respironics, Philips) will be used to measure the rest-activity rhythm, specifically sleep. Actiwatches are small activity monitors that are worn on the wrist, like a wristwatch, 24 hours a day. The Actiwatch gathers data by measuring the amount and intensity of movements made within every 5 seconds (which is the chosen epoch length). The Actiwatch stores the movement data of each epoch separately, which is retrieved later using a reader connected to a PC. The device's wristwatch-like design reduces physical discomfort to a minimum.

The Actiwatch provides information on the (in)stability of the rest-activity rhythm from one day to another (Inter-daily Stability; IS), and on the fragmentation of the rest-activity rhythm within the day, i.e. changes from periods of rest to activity and vice versa (Intra-daily Variability; IV). It also indicates the difference between maximal activity and maximal rest (Relative Amplitude; RA), and provides data on the 10 most active hours (M10) and the 5 least active hours (L5; for detailed information about these measurements, see the following references
^37,
38^).

Sleep analysis software (Philips Actiware 6.0.4, Respironics Inc.) will be used in order to analyse sleep. Sleep analysis will produce variables such as time spent in bed, sleep efficiency, sleep onset latency and total sleep duration.

*Sleep-wake diary.* Sleep-wake diaries are used to assess several events/activities such as time of medication use, use of caffeine/nicotine, bed time, wake time and time spent exercising. The sleep-wake diary is mainly used to improve the accuracy of sleep analysis.

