### Sample size calculation

A sample size calculation was made using G*Power version 3.1.3
^50^. Since no similar studies have been conducted, the effect size was set small-to-moderate (
*f* = 0.15). The lowest test-retest correlation of one of the used CANTAB tests was used as input for the correlation between repeated measures (r = 0.6).

In sum, effect size was set to
*f* = 0.15, with an alpha error probability of
*p* = 0.05, power of 1-β = 0.8, 1 group, 2 moments of measurement and correlation among repeated measures of r = 0.6. In G*Power, this resulted in a total sample size of N = 72.

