## Discussion

The main purpose of this study will be to investigate the influence of Running Therapy on executive functioning, sleep and aggression of prisoners. To our knowledge, this will be the first study of its kind in a prison population, which may provide results that are relevant to prison administrations, policymakers, and prison clinicians.

Different aspects of Running Therapy may have a positive influence on the prisoner population. Firstly, regular exercise may positively influence executive functions, in particular impulse control
^13,
14^, which could be of importance in reducing recidivism. Secondly, acute bouts of exercise may also improve executive functions such as attention, memory, reasoning and planning
^15,
51^, also making Running Therapy of added value in the short term. For example, it may be useful to plan Running Therapy sessions right before other activities or therapy sessions to improve attentional performance and increase participation of the prisoners. Furthermore, although investigating the influence of Running Therapy on depressive symptoms is a secondary objective of the current study, Running Therapy may have significant clinical impact on these symptoms as well. In general, aerobic exercise has a small-to-moderate effect on depressive symptoms
^32,
52^, which could improve cognition, sleep, and general well-being.

As antisocial personality disorder is highly prevalent in prison (65%)
^53^, this study may also be the first to examine the effects of exercise on the cognition of people with antisocial personality disorder. As impulsivity and/or failure to plan ahead is a clinical hallmark of these patients
^54^, improving executive functions such as impulse control or planning may be of added value in treatment.

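### M10 and relative amplitude, listed under the primary outcome Sleep, rise from the running itself, and no interval is set between the last run and the post-treatment CANTAB

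*Protocol article*

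**What the plan says.** All references are to the protocol article.

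- **Timing.** Measurements and procedures places baseline before the therapy starts and the post-measurement after 3 months of it. The Actiwatch is optional and worn for 7 consecutive days each time. Intervention describes two supervised runs and one unsupervised run a week. The goal of 30 continuous minutes three times a week is reached after 15 weeks.
- **Sleep outcome.** The Sleep part of Primary outcome measures has the watch worn around the clock and says that it "provides data on the 10 most active hours (M10"), together with L5, RA, IS and IV. It describes IV as fragmentation of the rhythm. The same part lists time in bed, sleep efficiency, sleep onset latency and total sleep duration. The diary covers "bed time, wake time and time spent exercising", mainly to make the sleep analysis more accurate.
- **Analysis.** Statistical analysis compares baseline with post in a single group, for the CANTAB results and for a set of sleep variables that it does not name one by one.
- **Acute effect.** The Discussion states that "acute bouts of exercise may also improve executive functions such as attention, memory, reasoning and planning". The scheduling statement for testing is that "the measurements will be planned during the moments in which participants are usually spending time in their cell"; no interval from the last run is given.

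**The concern.** M10 and RA are built from 24-hour movement. If the post week contains runs and the baseline week does not, the intervention changes these two indices directly, whatever happens at night. They stand under a primary outcome meant to answer whether running improves sleep, so a positive result could show only that the men ran.

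The CANTAB has a related problem. The protocol itself says that a single bout of exercise may improve abilities that the battery tests (planning, memory, attention). A post test can follow a therapy run; a baseline test cannot. With one group, no comparator absorbs the difference. The rationale is reoffending after release, for which a short-lived post-exercise effect is not the gain of interest.

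**Working it through.** **1. The plan's own figure.** Inputs from Sample size calculation: f = 0.15, alpha = 0.05, and "power of 1-β = 0.8, 1 group, 2 moments of measurement and correlation among repeated measures of r = 0.6". For a within-subject factor with m measurements, lambda = f² × N × m / (1 − r), with m − 1 and (N − 1)(m − 1) degrees of freedom. At N = 72, lambda = 0.0225 × 72 × 2 / 0.4 = 8.1 and power is 0.802. N = 71 gives 0.796. The statement that "this resulted in a total sample size of N = 72" is reproduced. The sample size is not in question; the same test is used in step 5.

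**2. Timing.** Three months is 365.25 / 12 × 3 / 7 = 13.0 weeks, against 15 weeks for the programme. Baseline questionnaires are brought to the first therapy day, which the Discussion puts a week later, so the baseline Actiwatch week appears to precede running. The post week appears to lie within a schedule of three runs in 7 days. Both points are inferred from stated durations; the article does not state them outright.

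**3. M10 and RA.** Assumptions not in the document: 30-minute runs, running counts at 5 to 10 times the usual daytime rate, baseline L5 at 10% of M10, nights unchanged.
- Running time: 3 × 30 / 7 = 12.9 min/day, which is 12.9 / 600 = 2.14% of the 10-hour window.
- Rise in M10: 2.14% × (5 − 1) = 8.6%, to 2.14% × (10 − 1) = 19.3%.
- RA = (M10 − L5) / (M10 + L5). Before: 0.9 / 1.1 = 0.818. After: 0.986 / 1.186 = 0.831, to 1.093 / 1.293 = 0.845. The change is 0.013 to 0.027.
- The 30-minute goal belongs to week 15. If runs last 20 minutes at week 13 (assumption), M10 rises by two thirds as much: 5.7% to 12.9%.

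**4. All indices, by simulation.** The standard nonparametric definitions were applied to 7 × 24 hourly values. Assumptions: waking level 100 and night level 8 counts per hour, lognormal noise with SD 0.3 or 0.6, three 30-minute runs a week adding 3 to 10 times the waking rate at a fixed or varying hour, sleep unchanged.

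| Index | Change due to the runs alone |
|---|---|
| M10 | +5% to +21% |
| RA | +0.006 to +0.023 |
| L5 | none |
| IV | +0.01 to +0.70 (more fragmentation) |
| IS | −0.36 to −0.01 in most scenarios; −0.01 to +0.01 with noisy days and a fixed hour |

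IS rose clearly (+0.22) only when runs took place every day at the same hour, which is not this programme.

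**5. CANTAB.** The document gives no size for an acute effect, so the mean shift d (in SD) is assumed. With r = 0.6, the standardised paired difference is d / √(2 × 0.4), and the noncentrality at N = 72 is that value × √72.

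| Mean shift over all 72 men | Probability of p < 0.05 |
|---|---|
| 0.086 SD | 0.13 |
| 0.1 SD | 0.15 |
| 0.2 SD | 0.46 |
| 0.3 SD | 0.80 |

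The rows for 0.1 SD and above treat the shift as the average over everyone. If an acute gain of 0.2 SD existed and only 3 in 7 post tests followed a run (assumption), the average would be 0.2 × 3/7 = 0.086 SD, which is the first row.

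**The case against.** The strongest case on the other side has five parts.

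- **The Sleep outcome already contains sound measures.** Sleep efficiency, onset latency, total sleep duration and L5 are listed, and the rhythm sentence only describes what the device delivers. Which variables are tested could be settled in an analysis plan that is not shown. The first part stands, and the fix builds on it. The second does not remove the point, because the article itself places M10 and RA under the primary heading and draws no line between them and the sleep variables.
- **The direction is mixed.** A reader might infer that all four indices rise and favour the therapy. Step 4 does not support that. Runs on 3 of 7 days usually lower IS or leave it flat, and a higher IV means a more fragmented rhythm. This stands in full.
- **Running at the post week is inferred.** Men removed for injury or aggression stay in the intention-to-treat analysis and may not be running. Fixed running days are not stated, and one run is unsupervised. This stands, and it would dilute the average effect.
- **The acute CANTAB effect is possible, not shown.** The text does not say that tests follow a run, and other sport before a baseline test is not excluded. This stands.
- **Testing on treatment is legitimate in a pilot.** The hypothesis promises no gain after therapy ends, and the Discussion counts acute benefit as part of the therapy's value. This also stands; the issue is only that the two sources of gain cannot be told apart.

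**Conclusion.** The point holds in a limited form and is a cheap improvement. M10, and through it RA, increase mechanically from the intervention with sleep unchanged, so a rise in them should not be read as better sleep. The size depends on run length and intensity, which are assumed here. The direction follows from the definitions, provided that the post week contains runs and the baseline week does not. IS and IV are disturbed as well, in a direction that depends on the running schedule and is often unfavourable to the therapy.

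Two stronger readings are tempting. One is that the primary sleep outcome as a whole is biased towards the hypothesis. The documents do not support it, because the night-time variables listed there are not mechanically raised by daytime running, and IS and IV tend to move the other way. The other is that a CANTAB gain would be an acute effect. The documents support only that such a contribution could not be separated from training. The probability of 0.46 at 0.2 SD needs that average shift across all 72 men, and nothing in the text establishes it.

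**What to change.** 1. Let sleep efficiency, onset latency and total sleep duration carry the primary sleep question. The software already produces them.
2. Reclassify M10, RA, IS and IV as secondary activity or rhythm measures. Add a sensitivity analysis that masks running periods where the diary or session times give clock times; a diary entry with only a duration will not allow it.
3. Record hours since the last run at the post CANTAB, since this cannot be reliably reconstructed later. Where feasible, hold that test on a non-running day.

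**Cost.** Items 1 and 2 relabel outcomes and use data already collected; the price is fewer rhythm indices among the primary outcomes. Recording the hours adds one field. A non-running day removes up to three days a week in a setting where the Discussion already reports difficulty in scheduling, so it should be a preference and not a strict rule.
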